## Design

To assess the implementability and proximal effects of the Kort intervention, we will use a mixed-methods combination including an intensive longitudinal time series and a quasi-experimental pre-post design. Qualitative data will be collected using individual interviews with adolescents, focus group interviews with school nurses, and audio recordings of consultations between school nurses and adolescents. Quantitative data will be collected using pre- and post-questionnaires and experience sampling measures (daily diaries and ecological momentary assessments; EMA).

To test how the combination of daily diaries and EMA will affect response rates we will conduct a two-arm micro trial within the study where adolescents are randomized to either daily diary sampling only (one measurement per day), or daily diary and EMA (between one and four measurements per day).

### Procedures

#### Recruitment

School school nurses will be convenience sampled through social media outreach and through a network of Norwegian municipalities organized by the study partner Fremsam, the Norwegian faction of the World Health Organizations’ Healthy Cities Network [44]. School nurses and leaders of school health services expressing interest will be invited to online information meetings. The leader of the school health service must sign a collaboration agreement before their school nurses can provide informed consent for participation.

The school nurses will be responsible for recruiting 1–5 eligible adolescents each and obtaining signed consent forms from the adolescents and their primary caregivers. Eligible adolescents will be identified through the mandatory 8th -grade consultation or by self-initiating support from a school nurse. Recruitment takes place in the following steps for adolescents under the age of 16:

The nurse determines whether the adolescent is eligible (mild to moderate mental health challenges).If eligible, the school nurse provides the adolescent with oral and written information about the Kort study and invites them to participate.If the adolescent consents orally, information and consent form will be distributed to the primary caregiver(s) by the school nurse via an SMS containing a link to the study’s website with additional information. The adolescents also receive an information pamphlet to take home with information and a QR code to the study’s website.On the website, the caregiver can give informed consent for both caregivers or only for themselves and provide contact information for the other caregiver.If applicable, an SMS is then sent to the other caregiver with information and a link to the website and consent form.

If the adolescent is aged 16 or older, steps a and b will be the same. In step c, if the adolescent consents orally, information and a consent form will be distributed to the adolescent by the school nurse via an SMS containing a link to the study’s website and a consent form with information tailored to their age group. The adolescent receives a pamphlet to take home, with study information and a QR code to the study’s website. Informing parents about the study is voluntary. Adolescents may be recruited consecutively throughout the study period and until two months prior to the end of the study.

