**Methods:**

The study employs a mixed-methods approach, integrating intensive longitudinal experience sampling (daily measures for 13 weeks), a micro trial, pre-, post-, and follow-up measures, audio recordings, and qualitative interviews to triangulate data from school nurses and adolescent participants. The research questions span the domains of intervention implementability, barriers and facilitators to implementation, proximal outcomes for adolescents’ emotion regulation, the mechanisms driving the intervention’s proximal effects, and response burden in experience sampling. The study aims to recruit a minimum of 25 health nurses and 46 adolescents.

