### Data collection and outcomes

Table 3 depicts outcomes, instruments, data collection methods, informants, and time points for all measures used in the study. The time points correspond to two weeks prior to the start of the intervention (T1), once the adolescent completes the intervention (dynamic post measure, T2), 11 weeks after the intervention begins (T3), and again 11 weeks after T3 (T4) to serve as pre- post- and follow up assessments, respectively. The experience sampling measures will have a two-week baseline assessment between T1 and the intervention start.

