The findings from this study can contribute to the development of scalable, efficient, and context-appropriate mental health interventions in school nursing. Also, the findings can advance the field of adolescent mental health by addressing critical gaps in intervention and implementation design. The study started recruitment in September 2023 and the study will end December 2024.

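### Recruitment may run to two months before study end, but T3 falls 13 weeks and T4 24 weeks after T1, so late recruits lose T4 (and the latest also T3) unless collection continues past that end

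*Protocol article*

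**What the plan says.** **Entry rule.** The Recruitment section states: "Adolescents may be recruited consecutively throughout the study period and until two months prior to the end of the study".

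**Calendar.** The Discussion states: "The study started recruitment in September 2023 and the study will end December 2024". The article does not say whether that end refers to recruitment, delivery by the nurses, or the last questionnaire.

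**Measurement schedule.** Data collection and outcomes places T1 two weeks before the intervention starts and T2 at a variable point: "once the adolescent completes the intervention (dynamic post measure, T2"). The fixed assessments come "11 weeks after the intervention begins (T3), and again 11 weeks after T3 (T4) to serve as pre- post- and follow up assessments". The same section adds: "The experience sampling measures will have a two-week baseline assessment between T1 and the intervention start". The Abstract describes "intensive longitudinal experience sampling (daily measures for 13 weeks"). The note to Figure 2 ties T3 to the end of experience sampling and T4 to 11 weeks after that.

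**A competing length.** The section on adolescents' proximal emotion regulation calls the experience sampling period two months, not 13 weeks.

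**Use of the data.** DERS-SF, BFS and SWEMWBS at T1 to T4 stand under the primary outcome measures. Quantitative analyses compares pre, post and follow-up means by repeated measures ANOVA and handles missing values at these timepoints by multiple imputation.

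**The concern.** The entry rule leaves less time than the measurement schedule needs. Followed as written, with collection closing at study end, it admits adolescents whose T4 can never be observed and, among the latest, whose T3 cannot be observed either.

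T4 is the only assessment described as follow-up. T3 is the only post measure for the scales that Table 3 does not collect at T2: mental health literacy, mindfulness, cognitive fusion, functional impairment, loneliness, self-compassion, sleep and friendships.

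The loss would be fixed by entry date and would add to ordinary dropout. The analysis section does not separate values that the calendar made unobservable from values that were not returned, so both would go to multiple imputation.

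**Working it through.** **1. Schedule, counted from T1**
- T1 to T3 = 2-week baseline + 11 weeks = 13 weeks. This reproduces the 13 weeks of daily measures in the Abstract.
- T1 to T4 = 13 + 11 = 24 weeks.

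**2. Time left at the cut-off**
- Two months = 2 × 30.44 / 7 = 8.7 weeks.
- Shortfall for T3 = 13 − 8.7 = 4.3 weeks.
- Shortfall for T4 = 24 − 8.7 = 15.3 weeks.
- If there were no baseline and the intervention began on the day of recruitment, T3 would still be 11 − 8.7 = 2.3 weeks late.

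This takes T1 as the day of recruitment. Any delay between the two makes the shortfall larger.

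**3. Calendar dates**

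| Study end (assumed day) | Last recruitment allowed | Last T1 that allows T3 | Last T1 that allows T4 |
|---|---|---|---|
| 1 December 2024 | 1 October 2024 | 1 September 2024 | 16 June 2024 |
| 31 December 2024 | 31 October 2024 | 1 October 2024 | 16 July 2024 |

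An adolescent with T1 on 31 October 2024 would reach T3 on 30 January 2025 and T4 on 17 April 2025.

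**4. Share of recruits affected.** The article gives no accrual curve. Even accrual is an assumption here, as is a total of exactly 46 filling the whole window.
- Window 1 September 2023 to 31 October 2024 = 426 days.
- T3 missed: 30 / 426 = 7%, and 0.07 × 46 = about 3.
- T4 missed: 107 / 426 = 25%, and 0.25 × 46 = about 12.
- With no recruitment from mid-June to mid-August (61 days, of which 30 fall after 16 July), T4 missed: (107 − 30) / (426 − 61) = 77 / 365 = 21%, about 10 of 46.
- Moving the start within September 2023 and the end within December 2024, without a pause, gives 7–8% for T3 and 25–29% for T4.

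**5. Combined with the 15% dropout allowance**
- 25% case: 46 − 12 = 34, and 34 × 0.85 = about 29 with T4.
- 21% case: 46 − 10 = 36, and 36 × 0.85 = about 31 with T4.

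**6. What the cut-off recruit still supplies.** From 31 October to 31 December is 61 days: 14 of baseline and 47 after the intervention starts, out of 13 × 7 = 91 planned. The power calculation uses 10 or 20 points on each side. T2 is obtained if the adolescent completes the intervention within 8.7 − 2 = 6.7 weeks of starting.

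**7. The two-month sampling period.** If T3 followed an 8.7-week sampling period that began at recruitment, it would just fit. T4 would then fall at 8.7 + 11 = 19.7 weeks and still not fit. That reading also conflicts with the 13 weeks in the Abstract and the 11 weeks in Data collection and outcomes.

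**The case against.** **The end of the study is not defined.** The implementation strategies speak of the study and the study period in connection with nurse training and supervision. On that reading, the cut-off leaves two months to deliver a brief intervention, and scheduled questionnaires could follow later. Data deposit is planned only for December 2026. This stands as a real ambiguity: if collection continues, the loss disappears. But nothing in the article says that it continues.

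**A reader might infer that late recruits supply no post outcome at all.** The documents do not support this. T2 is a dynamic post measure and carries DERS-SF, BFS and SWEMWBS.

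**A reader might infer that the sample size is undermined.** It is not. The 46 is derived for daily diaries, late entry costs no baseline days, and these adolescents can properly count towards it. The article states no power requirement for T4.

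**A reader might take 34 or 29 as a ceiling on T4.** The 46 is a minimum, and accrual may be uneven or finish early. The figures illustrate one assumption.

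**A reader might conclude that these values must not be imputed.** Missingness fixed by entry date is plausibly ignorable once entry date is in the model. A complete-case repeated measures ANOVA would also discard late recruits' observed T1 and T2. Separate reporting is the firmer request.

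**An earlier stop to recruitment has a price.** It would give up autumn-term recruits whose diary data are useful, so it is a trade-off and not the obvious remedy.

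**Conclusion.** The entry rule and the measurement schedule do not fit together as written. The 13-week, 24-week and 8.7-week figures come directly from the protocol. That the late assessments are actually lost rests on one condition: that the December 2024 end is the end of data collection.

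On that condition and under even accrual, the T4 loss is about a fifth to a quarter of the minimum sample (up to 29% for other start and end days within the stated months). That is larger than the only loss the plan allows for and is added to it. The T3 loss is about 3 or 4 adolescents and matters mainly for scales without T2. The diary analysis and the T2 results for the three main scales are largely untouched.

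**What to change.** Reconcile the Recruitment cut-off, the T1 to T4 schedule, the two-month sampling period and the December 2024 end date. The direct way is to define the end of data collection as the T4 of the last enrolled adolescent, and to keep the automated diary, T3 and T4 prompts running for those already enrolled. For a recruit at the end of October 2024 this means until about mid-April 2025.

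The cost is a few sentences in the protocol and about three and a half more months of automated questionnaires. The accumulated gift card is awarded at study end, so its timing would need to follow the new definition. The December 2026 data deposit is not affected.

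If collection must close in December 2024:
- state that adolescents entering after the dates above will not contribute T4 (or T3);
- report the number lost for this reason separately from dropout;
- include entry date in the imputation model, or add a sensitivity analysis limited to adolescents who could have reached the timepoint.

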#### Intervention development

The development of the Kort intervention followed three distinct steps: (1) Evidence synthesis, (2) theoretical development and modeling, and (3) human-centered element-based co-design and prototyping.

##### Step 1: evidence synthesis using systematic common elements reviews

We conducted two systematic common elements reviews to identify discrete intervention elements associated with effects on adolescents’ emotion regulation. One review [11] synthesized and distilled the literature on adolescents with identified mental health problems (symptoms meeting diagnostic criteria) or indicated mental health problems (subclinical levels or symptoms). The other currently unpublished review synthesized and distilled the literature on brief interventions for adolescents (10 sessions or less). The reviews identified 16 distinct common intervention elements associated with improved ER, which was taken into step 2.

##### Step 2: theoretical development and modelling

We consulted the systematic reviews and their primary studies and intervention manuals for details about how, when, and for whom the 16 elements were used when they were associated with improved ER. We also consulted the literature and expert opinions for theoretical explanations of the effects. These inputs formed the basis for conceptual models theoretically explaining how each element could improve ER: through what mechanisms and processes could they improve ER, and which determinants are likely to be influential or necessary.

##### Step 3: element-based co-design, prototyping, and usability testing

We developed prototype intervention protocols for each of the 16 discrete elements based on evidence and information from steps 1 and 2. These prototypes were used as inputs in a series of 13 workshops throughout 9 months. In these workshops, we used co-design methods and principles tailored toward ensuring implementability and effectiveness within the natural practice of school health services. The workshops were modeled after an approach developed for a former study, described in detail in Engell et al. [33]. In short, we used *element-based co-creation* [45] to inform a principle, ethics, and value-driven approach to co-design evidence-informed practices together with stakeholders (i.e., school nurses, adolescents, and intervention specialists). Also, we used the *Discover*,* Design*,* Build*,* Test Framework* for data-driven rapid cycle testing to iteratively resolve usability issues, reduce/simplify elements and tasks, and optimize the implementability of all final elements in the intervention [46]. Co-design activities included a common language exercise [33] and iterations of discussions, cognitive walkthroughs, role plays, usability testing and scoring, empathizing, ideation, and refining prototypes. The result was the intervention named *Kort* (Norwegian for *Brief*). A manuscript is in preparation, reporting complete details and data from the co-design process and results from interviews with co-design participants.

### The intervention Kort: elements, functions, and components

Kort is a flexible element-based intervention used through individual consultations between adolescents and school nurses. As depicted in Table 1, the intervention includes six core elements (abbreviations in parentheses): (1) Setting and reviewing goals (Goals), (2) Explore emotions, thoughts, and reactions in the body and how they are connected (Psychoeducation), (3) Explore and implement positive activities (Positive activities), (4) Practicing exposure to emotions (Exposure), (5) Practicing cognitive restructuring (Cognitive restructuring), and (6) Practicing mindfulness and stress management (Mindfulness). Practicing acceptance of emotions as an ER strategy is a key principle throughout the intervention. Each core element has 2–4 core functions hypothesized as the mechanisms, processes, or proximal outcomes through which the elements assert their effects on ER skills. These ER skills are subsequently theorized to prevent mental health issues, improve coping, and/or reduce early mental health issues. Achieving these core functions is the main focus of Kort. Each core element consists of 2–4 intervention components (activities, exercises, and processes) that, through research, theory, and co-design, have been found likely to contribute to achieving the elements’ core functions. Elements, functions, and components are depicted in Table 1. The complete intervention handbook is available upon request.

**Table 1 Tab1:** Core elements, functions, and components in the Kort-intervention

Core elements	Functions *What to achieve with adolescents*	Components *Evidence-informed “go-to strategies” for achieving functions*
Goals	1. Ownership of one’s own goal 2. Motivation 3. Targeted plan	1. Empower the adolescent to set personal goals 2. Follow up and adjust the goals of the adolescent
Psychoeducation	1. Knowledge about mental health 2. Normalization of feelings and thoughts 3. Familiarity with one’s own feelings and thoughts 4. Familiarity with acceptance as emotion regulation	1. Explore thoughts, emotions, bodily responses, behaviors, and how thet are connected 2. Use stress as an example of how thoughts, emotions, bodily responses, and behavior are connected 3. Explore acceptance of thoughts and emotions
Positive activities	1. Become aware of positive activities in one’s own life. 2. Increase the number of positive activities in everyday life	1. Exploring (health-promoting) activities in the adolescent’s life that make them happy/have positive feelings 2. Implementing more positive activities in the adolescent’s life (generally and/or strategically as regulation)
Exposure	1. Feasible exposure plan 2. Experience that emotions are not dangerous 3. Realize that intense emotions pass	1. Exposure planning 2. In vitro exposure 3. In vivo exposure
Cognitive restructuring	1. Familiarity with one’s own maladaptive thought patterns (thinking traps) 2. Breaking free of thinking traps 3. Experience good alternatives	1. Explore thinking traps 2. Challenge thinking traps 3. Cost-benefit analyses 4. Find better alternatives 5. Make a nudge or memo-rule
Mindfulness	1. Increase awareness 2. Regulate/manage stress 3. Regulate/manage challenging emotions	1. Breathing exercise 2. Mindfulness exercise (anchoring, body scan) 3. Relaxation technique

“Elements” are similar to “modules”, and are in themselves meaningful intervention entities (i.e., they do not depend on other elements to be valuable to use). “Functions” are the immediate or emerging processes, mechanisms, or outcomes the element aims to influence. “Components” are discrete activities and processes that are likely, based on evidence and stakeholder input, to help achieve functions, but they depend on other components to compose meaningful intervention entities. See Engell et al. [47] for details about the logic behind this nomenclature

#### Personalization and flexibility

The intervention structure is modeled after the principles of *Flexibility for Function* [33]. This is an operationalization of evidence-based practice through the ethically conscious integration and interdependence of evidence-based intervention elements, functions, and components, professional skills and autonomy, and optimizing personalization and adaptations. The training and handbook include specific sequences and combinations of elements that are considered helpful for different types of challenges adolescents typically face. However, school nurses will be trained in and encouraged to personalize the structure to the adolescents’ needs/goals, circumstances, and preferences, as well as making adjustments based on progress. Also, school nurses will be trained to defer to the components of each element as evidence-informed go-to strategies for working towards achieving the elements’ core functions. However, they are also encouraged and trained in making what they consider optimizing adaptations to these components (i.e., adaptations that increase the likelihood of achieving core functions) based on both planned and in-the-moment considerations of individual and contextual circumstances.

#### Implementation planning

In the exploration and preparation phase of the study, a pre-implementation study was conducted to (1) identify barriers and facilitators to, and potential consequences of, implementation of mental health interventions in school health services in general and the Kort-intervention in particular (research question 2.1), and (2) co-design implementation strategies that solve barriers, utilize facilitators, and minimize unintended consequences (research question 2.2). Table 2 summarizes the implementation planning process, and a manuscript presenting results on research questions 2.1 and 2.2, is in preparation.

**Table 2 Tab2:** Main activities in implementation planning

Step	Activity	Details, measures, theories, and tools
1	Recruit school nurses for implementation planning	
2	Quantitative assessment of implementation determinants	Quantitative measures of intervention appropriateness and feasibility [48], Usability [49], Implementation Intentions for each core element (MISII, [50]), Readiness for change, short version [51], self-efficacy and demographics
3	Analyses of assessment and development of interview guide	Descriptive analyses of data and development of semi-structured interview guide
4	Qualitative interviews about common barriers and facilitators to implementation and specific barriers and facilitators identified through quantitative assessment	Informed by the updated CFIR framework [52], COM-B theory [53], and implementability theory [33]
5	Qualitative focus group interviews with school nurses	Three digital 60 min interviews conducted by [name]
6	Individual interviews with leaders of school health services	Five interviews of 45 min. Theories above supplemented by specific reviews of theory and evidence about implementation leadership and climate [50, 54]
7.	Co-design workshops to develop implementation strategies	- Literature reviews of core elements of effective implementation practice [47] - Implementation strategy selection tool [45] - Facilitated brainstorming - Cognitive walkthroughs [46]
8	Causal modeling of: - Each implementation strategy using linear pathway diagrams and logic models - The complexity of all implementation strategies and the intervention over time using system dynamics modeling and calibration	- Causal pathway diagramming [55] - Micro-theorizing [56] - Causal loop diagramming and system dynamics modeling [57]
9	Iteration of step 7 to solve new barriers and consequences identified through system dynamics modeling	
10	Member checking and feedback meeting with school nurses and leaders	8 school nurses attended. Final adjustments of implementation strategies made

